### Primary and secondary outcomes

Our primary outcome is to report the epidemiology and associated outcomes of pediatric AKI worldwide (in over 30 PICUs, 12 different countries, 5 continents). This outcome is dependent on broad enrollment from participating centers. AKI is defined as KDIGO stage 2 or 3 AKI by creatinine and/or urine output criteria on Day 3 or later of PICU/CICU admission (Day 3 AKI).

Our secondary outcomes are to validate and refine the renal angina risk stratification model for prediction of Day 3 AKI.Determine if fulfillment of renal angina on Day 0 is predictive of severe AKI on Day 3 of PICU/CICU admission across the heterogeneous patient landscape of our participating centers. The AWARE data repository will be used to validate the precision of the RAI in ruling out AKI.Determine if prediction of Day 3 AKI by an RAI ≥ 8 is augmented by inclusion of urinary biomarkers alone or in combination.

Longer term outcomes to be followed include duration of mechanical ventilation, use of continuous renal replacement therapy, use of extracorporeal assist devices such as extracorporeal membrane oxygenation (ECMO) or ventricular assist devices (VADs), ICU length of stay, and mortality (Day 30 follow up).

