### Analysis

Analysis of data will be performed independently based on each specific aim.Data for the primary objective of describing the epidemiology of AKI will be presented as a descriptive model. The prevalence on day 0 and incidence of AKI in up to 7 days of ICU admission using KDIGO classification will be calculated for each site cohort to identify the geographical “hot spots” of pediatric AKI. The data then will be pooled into a single cohort to study the outcome of AKI. The whole cohort will be stratified on Day 3 into four sub-populations with: no AKI, AKI-KDIGO Stage 1, AKI-KDIGO Stage 2, and AKI-KDIGO Stage 3. An adjusted and unadjusted survival analysis models using log rank test and cox regression models will be used to compare the mortality rates and the need of renal replacement therapy between the 4 groups.The prognostic value of the renal angina index will be calculated on Day 0 for the development of Day 3 AKI. RAI will be evaluated as a diagnostic test and sensitivity, specificity, positive predictive value, negative predictive value, likelihood ratios, and receiver operating characteristics (ROCs) will be derived.Individual prognostic values of each of the four urinary biomarkers al one for Day 3 AKI will be calculated. The biomarkers will be tested in combination for changes in prognostic parameters and comparisons of discrimination using net reclassification improvement (NRI) and integrated discrimination improvement (IDI) will be derived. Finally, the contribution of each biomarker to the predictive model of renal angina for Day 3 AKI will be analyzed by integrating the biomarkers alone and in combination with the RAI.

Additionally, the association of renal angina index, urinary biomarker levels with clinical outcomes, including mortality, PICU length of stay, hospital length of stay, and renal replacement therapy provision, will be assessed using Chi-square test (or Fisher’s exact test for small counts) or Pearson correlation coefficient (or non-parametric Spearman correlation coefficient) based on the nature of data. Classification and regression tree analysis will be used to determine optimal decision rules for biomarker incorporation with RAI when discriminating for Day 3 AKI. In all analyses, a p-value of <0.05 will be considered statistically significant.

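### NRI and IDI p-values computed on the fitting data cannot decide at the 5% level whether a combination of biomarkers adds to the RAI

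*Protocol article*

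**What the plan says.** Under Primary and secondary outcomes, the article makes added value a secondary aim: "Determine if prediction of Day 3 AKI by an RAI ≥ 8 is augmented by inclusion of urinary biomarkers alone or in combination".

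The Analysis section then sets out the method in four steps:
- It starts with "Individual prognostic values of each of the four urinary biomarkers".
- It tests the markers in combination, where "comparisons of discrimination using net reclassification improvement (NRI) and integrated discrimination improvement (IDI) will be derived".
- It assesses their contribution to the renal angina model by "integrating the biomarkers alone and in combination with the RAI".
- It adds a tree: "Classification and regression tree analysis will be used to determine optimal decision rules for biomarker incorporation with RAI when discriminating for Day 3 AKI".

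The section closes with one rule for everything: "In all analyses, a p-value of <0.05 will be considered statistically significant".

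The Sample size section expects about 1,750 children with urine biomarkers.

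**The concern.** NRI and IDI summarise how predicted risks move when markers are added. The usual z-tests treat those predicted risks as given. They are in fact fitted, and the fitted coefficients follow whatever chance pattern the sample contains. Measured on the same children, the new model therefore tends to look better even when the markers are useless, so zero is the wrong reference value. The effect is small for one added coefficient and grows with each further one.

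The article's Background rests on small retrospective studies that already report better prediction once biomarkers are added to the RAI. AWARE is the large prospective test of that claim, so its analysis must be able to return a negative answer. If in-sample NRI or IDI at p<0.05 decides the matter, four worthless markers could be reported as augmenting the RAI.

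**Working it through.** **The plan's own figures.** 150 children per site × 35 sites = 5,250, and 5,250 / 3 = 1,750 with biomarkers. Both stated numbers reproduce. With the 31 or 32 sites given in the Abstract and under Setting, the biomarker set would be 31 × 150 / 3 = 1,550 or 32 × 150 / 3 = 1,600.

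**Inputs from the article.** n = 1,750; four biomarkers; significance at 0.05.

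**Assumptions, because the article gives no figure.**
- Two-sided testing.
- Event rate of Day 3 AKI 5-30%.
- RAI AUC 0.75, varied from 0.65 to 0.85 (the Background says only that discrimination is moderate).
- Standard published z-tests for NRI and IDI.

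**Method.** Outcomes and an RAI-like predictor were simulated, with biomarkers unrelated to the outcome. A logistic model with RAI alone and one with RAI plus the markers were fitted to the same children and compared there.
- Continuous NRI = [P(risk up) − P(risk down)] in events + [P(risk down) − P(risk up)] in non-events.
- IDI = mean change in predicted risk in events − mean change in non-events.
- Each is divided by its standard error and called significant if |z| > 1.96.
- Likelihood-ratio test (LRT): twice the difference in log-likelihood, referred to chi-square with as many df as added markers.

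**Share of studies with a false-positive result, n = 1,750:**

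| Situation | Continuous NRI | IDI | Either | LRT |
|---|---|---|---|---|
| One marker, tested once | 5.7-7.2% | 2.8-3.7% | 7.3-9.1% | not tabulated |
| Four markers together | 30-35% | 21-34% | 41-46% | about 4-6% |
| At least one of four single markers | 19-22% | 8-15% | 22-28% | 16-18% |

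The four-marker row combines two separate simulations. One used event rates of 5-30%. The other used 5-25%, with the RAI binary or continuous. The last row was run at event rates of 10% and 18%.

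**Precision.** Most settings used 1,500 simulated studies. At a rate of 30% the simulation error is √(0.30 × 0.70 / 1,500) = 0.012, or 1.2 percentage points. The last row used 600 studies per setting, which gives about √(0.20 × 0.80 / 600) = 0.016 at a rate of 20%.

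**Sensitivity, four markers together.**
- RAI AUC 0.65-0.85 at a 10% event rate: NRI 29-43%, IDI 16-32%.
- Markers correlated at 0.4: NRI 32-35%, IDI 24-25%.
- Log-normal markers: NRI 29-31%, IDI 20-27%.
- Sample size 500 / 1,000 / 1,750, at an assumed AUC of 0.78 and 12% events: NRI 35 / 37 / 38%, IDI 20 / 24 / 24%, LRT 4 / 6 / 5%. More children do not cure the problem, and the difference between 31 and 35 sites hardly matters here.
- Three-category NRI, assumed cut-offs at half and twice the event rate: 4% for one marker, 8-9% for four.

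**Where the fault lies.** With coefficients fitted on two thirds of the children and tested on the other third (10% event rate, four useless markers), NRI rejects in 6.0% and IDI in 5.9%. The inflation comes from testing on the fitting data.

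**Multiplicity alone.** For four independent valid tests at 0.05, 1 − 0.95⁴ = 1 − 0.8145 = 18.5%. The simulated LRT figure of 16-18% agrees, so a valid test still leaves the single-marker question in need of adjustment.

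**The case against.** **The link to p<0.05 is indirect.** The article says NRI and IDI will be derived and describes no test of either. The threshold comes from the closing sentence, and the sentence on integrating markers with the RAI names no metric. This stands as a caution: judging added value by NRI and IDI p-values is a reading of the text, though a natural one. NRI and IDI are the only comparison measures named, and the threshold is said to cover all analyses.

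**The inflation is not general.** This also stands. One marker tested once is close to 5%, with IDI below it. The type of NRI is not stated, and a categorical version is only mildly inflated. The large figures belong to continuous NRI and IDI with several markers. That is still the planned situation, because combinations are named in both the aim and the analysis.

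**Details may sit in an analysis plan.** Validation steps and multiplicity rules are commonly left there, and their absence from an article is no fault. The point therefore rests on the stated choice of measures and the flat threshold.

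Three stronger readings are tempting but not supported:
- A reader might infer that the tree is judged on the children who built it. The article says only "Classification and regression tree analysis will be used to determine optimal decision rules for biomarker incorporation with RAI" and is silent on how performance will be measured. A tree also has no p-value, so the 5% argument does not reach it.
- From the aim to "validate and refine the renal angina risk stratification model" a reader might infer that the RAI is validated without independent data. The cut-off of 8 is fixed in advance under Renal angina index calculation, and the Sample size section reports earlier work in 370 admissions at two sites. Applying a fixed rule to a new cohort is genuine validation.
- A reader might multiply error rates over a long list of independent tests. The article lists no such set, and marker subsets tested in the same children overlap.

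**Conclusion.** The concern holds for biomarker combinations. If in-sample NRI or IDI at p<0.05 decides added value, four useless markers would appear to help in about 41-46% of studies by at least one of the two measures, roughly eight to nine times the nominal 5% (41/5 = 8.2; 46/5 = 9.2). The likelihood-ratio test stays at about 4-6%. Separately, testing four single markers each at 0.05 gives about 16-18% for at least one false positive even with a valid test.

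These sizes assume a continuous NRI, the usual z-tests on the fitting data, an RAI AUC near 0.75 and an event rate of 5-30%. None of these is stated in the article. If a three-category NRI is meant, its own excess falls to 8-9%, but the IDI result is unaffected. The aim is secondary and the study observational, so this is a change that should be made rather than one that undermines the study.

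**What to change.** - **Main test.** Name one: RAI against RAI plus the four biomarkers, by a 4-df likelihood-ratio test in the same children, namely those with all four biomarkers measured. Fix beforehand how the RAI enters the model.
- **Single markers.** Test each marker added to the RAI afterwards, with Holm adjustment across the four.
- **NRI, IDI and change in AUC.** Report them as internally validated estimates with intervals and without p-values. State the type of NRI and any cut-offs.
- **Tree.** Label any decision rule from it exploratory and report its cross-validated performance.
- **Threshold sentence.** Limit the p<0.05 rule so that it no longer covers NRI and IDI.

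The cost is a few sentences in the analysis plan and some programming. No new data are needed. The reported gains from biomarkers will be smaller.

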### Inclusion criteria

The inclusion criteria are designed to capture as many potential study patients as possible and are inclusive of most patients admitted to the PICU and cardiac intensive care unit (CICU). All inclusion criteria must be met and only patients with an ICU length of stay of at least 48 hours are included in data analysis (other patient data is kept for demographic data repository, but excluded from data analysis for renal angina or AKI associated outcome).In-patient in a PICU or CICUAge ≥ 90 daysAge < 25 years

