### Sample size

The AWARE study will be the largest prospective *pediatric* AKI study describing global epidemiology, risk factors, and associated outcomes. To date, the largest prospective cohort study of AKI to date was conducted by the Beginning and Ending Supportive Therapy for the Kidney (BEST Kidney) investigators [34]. In the BEST Kidney study 18% of 29,269 patients prospectively studied after admission to 54 adult ICUs across 23 countries over 15 months developed AKI. For the AWARE study, we based our sample size estimation on the number needed to validate RAI internationally. We validated RAI in 370 PICU admissions from two different sites (average of 185 per site) in North America [5]. To be able to make RAI a universal index, we need to validate the RAI in all participating sites. Accordingly we are estimating the average number of enrolled children to be an average of 150 from each participating site with a total of approximately 5,250 children from all sites (assuming the final number of participating centers is around 35). Among the participating sites, we estimate one third to participate in urine collection, resulting in an expected approximately 1750 patients with urine biomarkers able to be measured. We are allocating each site 3 consecutive months to complete patient enrollment. Data capture can occur after the three months are complete, but no new patients are to be enrolled.

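### Correlating RAI and biomarkers with length of stay by Pearson or Spearman takes no account of death after 48 hours, which distorts the size of the estimate (minor, additional analysis)

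*Protocol article*

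**What the plan says.** The final paragraph of the Analysis section in the protocol article lists the outcomes to be related to RAI and the biomarkers as "including mortality, PICU length of stay, hospital length of stay, and renal replacement therapy provision". It names the tests: chi-square or Fisher's exact test, "or Pearson correlation coefficient (or non-parametric Spearman correlation coefficient) based on the nature of data". Length of stay is numeric, so it falls to one of the two correlation coefficients.

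Time-to-event methods do appear in the same section, but for another purpose. Across the four KDIGO groups, models "using log rank test and cox regression models will be used to compare the mortality rates and the need of renal replacement therapy". Length of stay is not among their endpoints.

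Two other statements bear on the point. The Inclusion criteria section says that "only patients with an ICU length of stay of at least 48 hours are included in data analysis". The Primary and secondary outcomes section lists, among the longer-term outcomes, duration of mechanical ventilation and "ICU length of stay, and mortality (Day 30 follow up").

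The article does not say how the stay of a child who dies enters the correlation.

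**The concern.** Death ends a stay, but not in the way that recovery does. A correlation with raw stay gives the same value to a child who dies on day 4 and a child discharged well on day 4. Moving from Pearson to Spearman does not help, because the two children then share a rank.

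The article's own premises make this more than a technicality. The Background section links AKI both to longer hospital stay and to a higher risk of in-hospital death. RAI and the biomarkers were chosen because they should predict severe AKI. The same children are therefore expected to stay longest and to die most often, and for those who die early the two effects pull the observed stay in opposite directions.

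At stake is the reading of the coefficient. A modest value could mean a modest predictor, or a good predictor whose highest-risk children left the ICU by dying. The reported figure would not separate the two.

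**Working it through.** **The plan's own figures.** The Sample size section gives "an average of 150 from each participating site with a total of approximately 5,250 children from all sites", assuming about 35 centres: 150 × 35 = 5,250. One third with urine samples: 5,250 / 3 = 1,750. Both reproduce. The article gives no figure for mortality, time of death, length of stay or its expected correlation with RAI. Every input below is therefore an assumption, shown over a range.

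**Model A: death cuts the stay short.** 400,000 simulated children per scenario.
- Predictor x: standard normal.
- Stay without death: 2 days + a log-normal time with median 4 days, slope 0.30 per SD of x and log-SD 0.8.
- Death: logistic in x, with the intercept set to give 5% mortality.
- Time of death: 2 days + an exponential time. All deaths thus fall after 48 hours, in line with the inclusion rule.
- Observed stay: the earlier of death and discharge.

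The Spearman correlation without deaths is 0.336. With deaths:

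| Mean death time after 48 h | Strong link to death (slope 1.2) | Share of 0.336 lost |
|---|---|---|
| 3 days | 0.264 | 1 − 0.264/0.336 = 21% |
| 6 days | 0.290 | 14% |
| 10 days | 0.305 | 9% |
| 14 days | 0.313 | 7% |

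With a weak link (slope 0.4), the range over the same death times is 0.302 to 0.325, a loss of 10% down to 3%. If the time of death replaces the stay instead of cutting it short, deaths at a mean of 14 days with the strong link give 0.337, which is no loss.

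**Effect of mortality in Model A** (slope 1.2, mean death time 3 days): about 0.29 at 3%, 0.20 at 10% and 0.15 at 15%.

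**Model B: different inputs, as a check.** Stay is log-normal with median 5 days, log-SD 0.8 and slope 0.25 per SD. Death has an odds ratio of 1.5 or 3 per SD. The time of death replaces the stay, and only stays of at least 48 hours are kept. Each cell gives the correlation with observed stay / the correlation among survivors:

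| Mortality, odds ratio | Median death 3 d | 6 d | 14 d |
|---|---|---|---|
| 2%, 1.5 | 0.226 / 0.235 | 0.230 / 0.235 | 0.235 / 0.234 |
| 5%, 3 | 0.192 / 0.232 | 0.220 / 0.230 | 0.263 / 0.227 |
| 10%, 3 | 0.151 / 0.225 | 0.204 / 0.222 | 0.289 / 0.226 |

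Early deaths attenuate the correlation. Late deaths can raise it above the survivors' value. With low mortality and a weak link, little changes.

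**Would the association be missed?** The smallest correlation that reaches two-sided p < 0.05 is about 1.96/√n.
- n = 5,250: 1.96/72.5 = 0.027.
- n = 1,750: 1.96/41.8 = 0.047.

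The lowest value in any scenario was 0.083 (Model B, 20% mortality, odds ratio 3, median death at 3 days), which exceeds both.

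**The case against.** The strongest reply is that the article is silent on deaths rather than wrong. It never says that a stay ended by death is counted as observed, and a fuller document may set a rule. That is fair as far as it goes: a reader might infer that the plan scores death as a favourable outcome, and the text does not say so. What remains is that the article does name the method. A correlation coefficient has no place for a competing event, so any rule that deals properly with death must change the outcome or the method named there. Restricting the analysis to survivors would fit the named method, but it answers a question conditional on survival and leaves out the worst outcomes.

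A reader might also infer that the correlation must be biased toward zero. The documents do not support this. They give neither mortality nor timing of death, and late deaths can leave the coefficient unchanged or above the survivors' value.

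Nor do they support the fear that a working predictor would appear to have no association. The planned numbers make even strongly attenuated correlations detectable under the stated rule, "In all analyses, a p-value of <0.05 will be considered statistically significant".

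Ranking death worst gives higher correlations in Model A: 0.36 to 0.44 as mortality goes from 3% to 15%, with mean death time 3 days. These are not the correct answer for length of stay. They describe a composite of death and stay, and they exceed the assumed 0.34 for that reason. Observed bed-days are also a legitimate measure of resource use.

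A further inference, that the distortion would spoil comparisons between sites, has little basis. The plan computes AKI frequency by site but pools the data to study the outcome of AKI, and it states no site-level correlation with stay.

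Finally, the stakes are limited. This is an additional analysis, mortality is tested in the same sentence, and the 48-hour rule removes the earliest ICU deaths. All of that stands. It lowers the weight of the point but does not correct the length-of-stay estimate.

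**Conclusion.** The point holds as a minor one. The method fixed for PICU and hospital length of stay cannot handle death after 48 hours, and the article's own premises tie the predictors to both stay and death. If death simply ends the stay, the coefficient is distorted. It is usually attenuated, most when deaths come early: from 0.34 to between about 0.26 and 0.31 at 5% mortality with a strong predictor–death link, on assumed inputs. The loss is smaller with a weak link, and little or none when deaths are also late. Direction and size cannot be fixed from the documents. The fault lies in how large the association appears and what it means, not in a false null result. The primary outcome and the validation of RAI for Day 3 AKI are not affected.

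**What to change.** Replace the correlation with raw stay, as the main length-of-stay analysis, by one of two options:
- time to discharge alive, for ICU and for hospital, with death as a competing event; or
- ICU-free days to Day 30, with death set to 0 and analysed by a rank method, labelled as a composite of death and stay.

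Name the chosen option before analysis. Keep observed stay (all children) and survivors' stay as descriptive figures, each labelled as such. If duration of mechanical ventilation is to be analysed in the same way, treat it likewise.

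The cost is a change of analysis wording and slightly more analysis. Length of stay and Day 30 mortality are already followed, so little or no new data should be needed. The downside is that either measure is less familiar to readers than length of stay.

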### Oversight

The Center for Acute Care Nephrology at CCHMC will oversee the AWARE trial from start to finish. The central data repository through RAVE™ will be housed at CCHMC. Each site will perform screening, enrollment, consenting (when applicable), processing the urine samples (when applicable), collecting and entering data to Rave™ web browser. The research personnel in every site will be able to access the data of children enrolled from the same site. Only CCHMC research personnel will have access to the data collected for the purposes of this study from all participating sites. CCHMC will be responsible for managing and analyzing the data and testing the urine samples for urinary biomarkers. All participating sites will use the same case report form (CRF). The web-based CRFs will be designed and monitored by the Medidata Rave™ representatives in the Data Management Core at Cincinnati Children’s Hospital Medical Center (CCHMC). As the project coordinators, the Center for Acute Care Nephrology (CACN) at CCHMC will be the only site that can access the data from all other sites. Other sites will have access only to their enrolled subjects. Data management and statistical analysis will be executed at CCHMC.

The AWARE study is a featured study of the Prospective Pediatric Acute Kidney Injury Registry (www.ppaki.org). Founded in 2012, the ppAKI is an international research consortium comprised of pediatric nephrologists and intensivists striving to foster development and advances in the research of pediatric acute kidney injury.

